## Abstract

**Background:**

Physical inactivity is fourth in the list of risk factors for global mortality. General practitioners are well placed to offer physical activity counseling but insufficient time is a barrier. Although referral to an exercise specialist is an alternative, in Australia, these allied health professionals are only publicly funded to provide face-to-face counseling to patients who have an existing chronic illness. Accordingly, this trial aims to determine the efficacy of GP referral of insufficiently active patients (regardless of their chronic disease status) for physical activity counseling (either face-to-face or predominately via telephone) by exercise specialists, based on patients’ objectively assessed physical activity levels, compared with usual care. If the trial is efficacious, the equivalence and cost-effectiveness of face-to-face counseling versus telephone counseling will be assessed.

**Methods:**

This three arm pragmatic randomized trial will involve the recruitment of 261 patients from primary care clinics in metropolitan and regional areas of New South Wales, Australia. Insufficiently active (less than 7000 steps/day) consenting adult patients will be randomly assigned to: 1) five face-to-face counseling sessions, 2) one face-to-face counseling session followed by four telephone calls, or 3) a generic mailed physical activity brochure (usual care). The interventions will operationalize social cognitive theory via a behavior change counseling framework. Participants will complete a survey and seven days of pedometry at baseline, and at three and 12 months post-randomization. The primary analyses will be based on intention-to-treat principles and will compare: (i) mean change in average daily step counts between baseline and 12 months for the combined intervention group (Group 1: face-to-face, and Group 2: telephone) and usual care (Group 3); (ii) step counts at 3 months post-randomization. Secondary outcomes include: self-reported physical activity, sedentary behavior, quality of life, and depression.

**Discussion:**

If referral of primary care patients to exercise specialists increases physical activity, this process offers the prospect of systematically and sustainably reaching a large proportion of insufficiently active adults. If shown to be efficacious this trial provides evidence to expand public funding beyond those with a chronic disease and for delivery via telephone as well as face-to-face consultations.

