### Sample size

A sample size of 79 participants per group will provide 90% power to detect a differential increase of 1000 steps per day at 12 months between the two intervention groups and the usual care group at the 5% significance level. This sample size was calculated assuming that the usual care group will increase their average daily step count by 1000 steps, and the standard deviation of 2500 observed in the pilot study. Attrition rates are estimated to be 10% over the twelve month period [60]. This results in a total required sample of 261 (n = 87 per group).

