### Statistical analyses

Baseline data will be summarized as the number of observations, means, standard deviations, medians, minimums and maximums where the data are continuous and as number of observations and frequencies where the data are categorical. The data will be presented separately by treatment group.

The primary endpoint (mean change in daily step counts from baseline to 12 months) will be analyzed using a constrained linear mixed model approach [61], where the outcome in the model is the mean number of steps per day at each time point, but the baseline mean responses for the treatment groups are assumed equal. This approach has been shown to be robust when missing data depend on baseline values [62]. Predictor variables in the model will include fixed effects for group (usual care as reference and group 1: face-to-face, group 2: telephone), time (baseline as reference, 3 months and 12 months) and the interaction between group and time. A subject level random intercept will be included in the model to allow for correlations arising from repeated measures. There may be some variation to this model after checking its underlying assumptions of multivariate normality, linearity and equal variance and clustering. The primary comparison will be between the combined intervention groups (group 1: face-to-face and group 2: telephone) and usual care. A secondary analysis will examine the difference in step counts at 3 months, and if significant differences are found in the primary analysis, will also explore if there are differences between treatment groups (face-to-face and telephone). Sub group analyses will be conducted by sex, BMI category and diagnosed chronic disease versus none. Sensitivity analyses will explore the impact of individual EP, GP clinic, and after removing the steps imputed from self-reported physical activity. The analysis will be conducted on an intention-to-treat basis with alternative methods of accounting for missing data: multiple imputation, and pattern mixture modelling [63].

Process evaluation will be assessed by calculating adherence with intervention (mean number of sessions completed, average time of intervention delivery for face-to-face and telephone counseling sessions). Intervention fidelity will be assessed by coding of EP checklists.

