## Discussion

The NewCOACH study is a three-arm pragmatic randomized trial that aims to determine the efficacy of GP referral of insufficiently active patients (regardless of their chronic disease status) for physical activity counseling (either face-to-face or predominately via telephone) by exercise specialists, based on patients’ objectively assessed physical activity levels, compared with usual care. If the trial is efficacious, the equivalence and cost-effectiveness of face-to-face counseling versus telephone counseling will be assessed.

Strengths of this study include the pragmatic design, the use of an objective measure of physical activity, the use of qualified exercise specialists (EPs) to deliver the theory-based behavior change counseling, and the 12 month follow-up to assess maintenance of behavior change. Limitations of the study include that only a sub-sample will provide accelerometer data.

If the physical activity counseling is efficacious, this will have implications for the design of future exercise referral schemes and EP funding models both in Australia and internationally. If the trial demonstrates that referral to an EP for coaching is an effective way to get people more active, it will be very attractive to GPs to make greater use of CDM pathways. Current funding legislation in Australia restricts CDM to those with an existing chronic disease [64]. If improvements in physical activity can be demonstrated for previously inactive but otherwise healthy adults in this trial, this will provide support for expansion in the eligibility criteria for the Medicare allied health initiative to include insufficiently active patients who do not have a chronic condition. This would be a significant shift away from just treatment of disease, and would acknowledge the role of allied health professionals in preventing disease in partnership with primary care clinicians. In addition, Medicare funding currently only recognizes face-to-face consultations. Evidence that telephone coaching is equally or more effective could lead to the funding of EP services for telephone delivery which would increase the reach and flexibility of this service.

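### The abstract draws a telephone-funding inference from overall efficacy, but efficacy is judged only on the two regimens pooled, which cannot show that the telephone regimen itself beats usual care

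*Protocol article*

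**What the plan says.** Protocol article, Statistical analyses: "The primary comparison will be between the combined intervention groups (group 1: face-to-face and group 2: telephone) and usual care". The Methods paragraph of the abstract describes the same pooled contrast, and the Sample size section is built on a "differential increase of 1000 steps per day at 12 months between the two intervention groups and the usual care group".

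The mixed model has usual care as the reference, a separate term for each regimen, and a group-by-time interaction. The only other contrast between arms that the section names is face-to-face against telephone. It is conditional on a significant primary result and framed as an exploration of differences. Telephone against usual care is not named.

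Two statements about telephone funding follow:

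- Abstract, Discussion paragraph: "If shown to be efficacious this trial provides evidence to expand public funding beyond those with a chronic disease and for delivery via telephone". The only condition is that the trial is efficacious.
- Main Discussion: "Evidence that telephone coaching is equally or more effective could lead to the funding of EP services for telephone delivery". Here the condition is comparative evidence between the two modes.

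The abstract, the aims at the end of the Background, and the main Discussion also promise an assessment of equivalence and cost-effectiveness of the two modes.

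**The concern.** The pooled contrast estimates the average of the two regimens' gains over usual care. It can be clearly positive when most of the gain comes from the face-to-face arm. The abstract nevertheless attaches the telephone inference to overall efficacy. The main Discussion says that Medicare currently recognises only face-to-face consultations, so telephone delivery is the part of the funding claim that most needs evidence of its own.

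The between-mode comparison does not fill the gap. Failing to find a difference shows neither that the modes are equivalent nor that telephone beats usual care. The two funding statements also rest on different conditions, so a reader cannot tell which result would support the telephone claim.

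**Working it through.** **Inputs from the Sample size section.** "A sample size of 79 participants per group will provide 90% power", a target difference of 1000 steps, "the standard deviation of 2500 observed in the pilot study", and testing "at the 5% significance level" with sidedness not stated. Equal arms of 79 completers are used throughout, with normal approximations.

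**Standard errors.**

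- Pooled (158) against usual care (79): 2500 × √(1/158 + 1/79) = 344.
- One arm against another (79 each): 2500 × √(2/79) = 398.

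**The plan's own figure.** Power of the pooled test at 1000 steps:

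- One-sided 5%: Φ(1000/344 − 1.645) = 89.6%, which matches the stated 90%.
- Two-sided 5%: Φ(1000/344 − 1.960) = 82.7%.

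The stated power therefore fits a pooled comparison at one-sided 5%. The two-sided level used below is an assumption.

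**Precision of the mode comparison.** The 95% CI half-width is 1.96 × 398 = 780 steps, or 78% of the 1000-step target. For the pooled contrast it is 1.96 × 344 = 675.

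**A hypothetical observed result.** Suppose the observed gains over usual care are 1000 (face-to-face) and 500 (telephone).

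- Pooled: 750, above 675, so significant.
- Mode difference: 500, below 780, so not significant; CI −280 to 1280.
- Telephone against usual care: 500, CI −280 to 1280, which includes zero.

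Both named contrasts would look favourable to telephone, while the contrast that bears on the claim would be inconclusive.

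**How often this could arise.** With equal arms and a common SD, the covariance of the pooled contrast and the mode difference is half of (variance of the face-to-face mean − variance of the telephone mean) = 0. Joint probabilities are therefore products: P(pooled significant) × P(mode difference missed). The true gains are assumptions; the article gives none by mode.

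| Face-to-face / telephone | Pooled significant | Mode difference detected | Pooled significant, difference missed |
|---|---|---|---|
| 1500 / 500 | 82.7% | 71.0% | 0.827 × 0.290 = 24.0% |
| 1200 / 300 | 58.6% | 61.9% | 0.586 × 0.381 = 22% |
| 1000 / 0 | 30.6% | 71.0% | 0.306 × 0.290 = 8.9% |
| 1500 / 0 | 58.6% | 96.5% | 0.586 × 0.035 = 2.1% |
| 2000 / 0 | 82.7% | 99.9% | 0.1% |

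In the 1500/500 case, telephone against usual care has about 24% power. If the pooled test is one-sided and the mode comparison two-sided, the joint figure is 0.896 × 0.290 = 26%.

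**If equivalence is formally tested.** The article gives no margin, so one is assumed. Two one-sided 5% tests at ±1000 declare equivalence when the observed difference lies within 1000 − 1.645 × 398 = 346 steps. With a true difference of 1000 the chance is about 5.0%, and jointly with a significant pooled test 0.0496 × 0.827 = 4%. The same calculation gives 0.7% at a margin of 750 and 13% at 1250.

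**Power of telephone against usual care at 1000 steps.** Φ(1000/398 − 1.960) = 71.0% two-sided; Φ(1000/398 − 1.645) = 80.8% one-sided.

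**The case against.** A reader might infer that the trial will recommend telephone funding on the pooled result alone. The article does not say that. The abstract says that the trial provides evidence, and the main Discussion says that such evidence could lead to funding. Neither is a fixed decision rule. Read as a whole, the plan has a second step: after efficacy, the modes are to be compared for equivalence and cost-effectiveness, and the main Discussion makes telephone funding depend on that comparison. This objection stands, and it confines the point to the abstract's condition and to what the named contrasts can show.

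The 24% is also open to challenge. It counts a non-significant mode difference as favourable to telephone, whereas the stated aim is equivalence; under a 1000-step margin the figure is about 4%. In that scenario telephone does work, only less well, and a truly null telephone arm would usually be exposed. These points stand too, so the 24% is an illustration and not a predicted error rate. But the Statistical analyses section describes a search for differences, and a ±780-step interval leaves a non-significant result open to misreading.

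Finally, telephone against usual care is already a coefficient of the planned model, and the list of tabulated contrasts can be left to an analysis plan not shown here. So the absence of a margin or of a table of contrasts is no fault. What remains is an inference in the article that its stated primary comparison cannot support, and two funding conditions that disagree.

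**Conclusion.** The point holds in limited form. The primary pooled test is unaffected. The abstract's telephone statement rests on overall efficacy, which the pooled test cannot translate into efficacy of the telephone regimen, and it differs from the condition in the main Discussion.

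The most secure figure is the ±780-step interval for the mode difference, which depends only on the plan's SD and completer numbers. The chance of a positive pooled test with the mode difference missed is about 22% to 24% for a weak telephone arm (1200/300 or 1500/500) and about 2% to 9% for a null one (1500/0 or 1000/0). These percentages assume the true gains and a two-sided 5% level. The documents do not support the stronger reading that an ineffective telephone regimen would commonly pass unnoticed. A change is worth making because it decides what the trial can say about telephone delivery.

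**What to change.** 1. After a significant pooled 12-month test, report face-to-face against usual care and telephone against usual care from the planned mixed model, each with a 95% CI. With two regimens this is a closed procedure: the pooled test is a valid test of the hypothesis that neither regimen works, so each regimen can then be tested at the full 5% level without splitting alpha.
2. Reword the Discussion paragraph of the abstract, and reconcile it with the main Discussion, so that the telephone inference rests on the telephone-versus-usual-care estimate read together with the between-mode comparison.

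This takes wording and two contrasts from a model already specified, with no new data and no change to the primary test. The cost in power is real. At 79 per arm, telephone against usual care has 71% two-sided power at 1000 steps (81% one-sided), so a telephone regimen delivering the full planned effect would miss significance in about 29% of trials. Reaching 90% two-sided would need 132 completers per arm. The telephone claim should therefore be stated through its confidence interval and not on significance alone.

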**Trial registration:**

Australian New Zealand Clinical Trials Registry ACTRN12611000884909.

## Background

Physical inactivity is fourth in the list of risk factors for global mortality [1]. In 2011–2012, fewer than 1 in 5 Australian adults met the threshold of 10,000 steps per day to confer a health benefit, with the mean (pedometer-assessed) step count being 7,400 steps per day [2,3]. As most (90%) Australian adults visit a General Practitioner (GP) at least once a year [4], GPs are well placed to provide physical activity counseling. However, evidence regarding the effectiveness of physical activity counseling by medical professionals is mixed [4-6]. Only behavioral counseling interventions involving greater than 30 minutes of total patient contact time have shown beneficial effects on behavioral and intermediate health outcomes, and only interventions with more than 360 minutes of total patient contact time reported sustained benefits beyond 12 months [6]. Effective physical activity counseling by GPs may not be feasible given that GPs generally identify a lack of time as a barrier to preventive counseling [7-14].

One alternative to physical activity counseling by GPs is the referral of patients to an exercise professional (variously referred to as ‘exercise on prescription’, ‘GP exercise referral’ or just an ‘exercise referral’ scheme). Although variations in delivery exist, exercise referral commonly involves a GP (or another member of the primary care team) identifying and referring a sedentary individual with evidence of at least one cardiovascular risk factor or existing chronic disease to a third party service (often a sports centre or leisure facility) [15]. This service then prescribes and monitors an exercise program (normally 12–14 weeks) often delivered at the sports/leisure centre [16]. In the United Kingdom, contemporary exercise referral schemes were first set up around 1990, with more than 600 schemes now in operation [17] all adhering to a core set of standards [18]. The exercise referral model is also being established in primary care practice in other parts of Europe [19,20] and is operationalized differently internationally. In New Zealand, referral schemes have tended to be delivered as part of ‘Green Prescription’ schemes administered through primary care settings with the support of trained telephone counselors [21,22]. The Green Prescription is based around achieving daily time-based activity goals and has been shown to be efficacious in increasing and maintaining physical activity 12 months post-prescription [21] and is cost-effective both in terms of relative cost per quality adjusted life year [23] and per successful treatment [24].

In Australia, the Federal Government has incorporated referral to Exercise Physiologists (EPs) as part of the government-funded Medicare scheme for adults with a diagnosed chronic disease (originally known as an Enhanced Primary Care Plan and now referred to as Chronic Disease Management (CDM) [25]). EPs are university qualified allied health professionals with skills in sports physiology and training and rehabilitation as well as in clinical exercise interventions for persons at high-risk of developing, or with existing chronic and complex, medical conditions and injuries. EPs that undergo additional supervised training and meet the accreditation criteria set by Exercise and Sports Science Australia (ESSA) are eligible to register with Medicare to provide subsidized services as part of CDM. Under CDM, GPs develop a care plan that includes referral to a range of allied health professionals with patients eligible for up to five Medicare-funded sessions with the identified allied health professionals in any calendar year. Patient eligibility for CDM is restricted to those with a chronic medical condition that has been (or is likely to be) present for six months or longer. Despite the availability of this program, only 1% of GP consultations are related to chronic disease management [4], and EP consultations occur at a national rate of 2.6 consultations per 1000 people [26]. There have been few evaluations of the efficacy or cost-effectiveness of the CDM planning and referral pathway [27-29].

A recent systematic review and meta-analysis of eight randomized controlled trials (5190 participants) assessing the impact of exercise referral schemes concluded that considerable uncertainty remains as to the efficacy of referral schemes for increasing physical activity, fitness or health indicators for people with or without a medical diagnosis, and whether they are an efficient use of resources [17]. The review authors concluded there was significant heterogeneity across the current trials and recommended the conduct of further trials of these schemes, particularly ones that incorporate theory-driven interventions [17]. In addition, since all but one of the included 8 trials relied on a self-report measure of physical activity, trials that use an objective measure of physical activity are required. All eight of the trials in the Pavey review [17] referred inactive patients to a structured, supervised exercise program that was typically 10–12 weeks in duration, and held at leisure centres, clinics, or parks. None of the trials utilized individual coaching by a qualified exercise professional, and the development of an individualized unsupervised exercise plan. Only three trials had follow-ups of 12 months, and none longer than 12 months.

Anokye and colleagues [30] examined the cost-effectiveness of exercise referral schemes and concluded that whilst they are associated with a modest increase in lifetime costs and benefits, the cost-effectiveness is highly sensitive to small changes in the effectiveness and cost of schemes. It is therefore important to evaluate the various models of referral and compare cost-effectiveness for different delivery modes (e.g., face-to-face, telephone).

The NewCOACH pragmatic randomized controlled trial described here has two aims. Firstly to determine the efficacy of GP referral of insufficiently active patients (regardless of their chronic disease status) for physical activity counseling by EPs (either face-to-face or predominately via telephone), based on patients’ objectively assessed physical activity levels, compared with usual care. Secondly to compare the equivalence and cost-effectiveness of face-to-face and telephone counseling.

## Methods

### Design

The study was a three arm, parallel group, individually randomized pragmatic trial designed to determine the effect of physical activity counseling by an EP for patients referred from primary care (see Figure 1). Follow-up assessments occurred three and 12 months post-randomization. A pragmatic trial (a term first coined by Schwartz and Lellouch in 1967) is a randomized controlled trial whose purpose is to inform decisions about practice [31]. The current trial was deemed pragmatic as it was: 1) examining the intervention when used in normal practice, had little restriction on participants (e.g., inclusion of overweight/obese participants or those with multiple comorbidities); 2) it was conducted in the usual primary care setting with no additional resourcing; 3) the intervention (exercise counseling) delivered by EPs was applied flexibly based on their professional judgement and the preferences of the participant, and; 4) the outcomes (physical activity behavior at 12 months, cost) are directly relevant to participants, healthcare providers and funders [31]. This protocol follows recommended reporting procedures [31,32].

